### 2.9. Data Collection, Management, and Retention

Across the study period, we will collect (1) feasibility measures, (2) preliminary efficacy measures, (3) covariates, and (4) qualitative interview data from older adults and their care partners (Table 3). Data will be captured through surveys, Fitbit/Fitabase activity monitoring, myACTIVEsteps.com engagement metrics, and Zoom-based interviews.

All data will be coded with unique study IDs and stored securely on access-restricted institutional servers, with access limited to authorized study personnel. No direct personal identifiers will be collected, and only de-identified data will be shared for analysis or future research. Data integrity will be maintained through standardized collection protocols, regular quality checks, and audit trails. Study data will be retained in accordance with institutional and federal requirements.

Participant retention will be promoted through proactive monitoring, reminders, and flexible follow-up scheduling. Even in cases of partial discontinuation, key outcomes will be collected when possible, including remote data capture for surveys and activity tracking.

### 2.10. Outcome Measures

Consistent with the study objectives, this pilot study includes two broad categories of outcomes: Feasibility Measures and Preliminary Efficacy Measures. The outcome variables, measurement metrics, and assessment time points are detailed below

Feasibility Outcome Measures:

The feasibility of the ACTIVE intervention will be evaluated in accordance with NIH guidelines for pilot studies [40], with a focus on recruitment, adoption, adherence, acceptability, fidelity, and retention (Table 3). Feasibility outcomes will be assessed separately by AD/ADRD status and by intervention and control arms.

Recruitment will be defined as the proportion of dyads recruited and randomized to the study, with a target of at least 75%. Adoption will be defined as the initial engagement in week one for smartwatch use, motivational text interaction, video-guided physical rehabilitation session initiation, and viewing educational videos, with a target of at least 75%. Adherence will be defined as sustained engagement during the three-week intervention period, with targets of at least 75% for days of smartwatch use, number of completed video-guided physical rehabilitation sessions, and number of educational videos viewed.

Acceptability will be assessed at weeks 5 and 9 using the System Usability Scale and the revised Technology Acceptance Model. The System Usability Scale is a 10-item survey (Cronbach alpha (α) = 0.90), and higher scores indicate higher usability of the specific study tool [49,50]. The revised Technology Acceptance Model is a 10-item scale (α = 0.89), and higher scores indicate greater acceptance of the specific technology [51,52]. The System Usability Scale and the revised Technology Acceptance Model surveys will be used to assess participants’ acceptability of (1.) the website (myACTIVEsteps.com), (2.) the Fitbit smartwatch, (3.) motivational texts, (4.) educational videos, and (5.) video-guided physical rehabilitation. Acceptability will be defined as a System Usability Scale score of at least 68 and a revised Technology Acceptance Model score of at least 4.0. [49,50,51,52]. Fidelity will measure the proportion of motivational and educational text notifications successfully delivered, with a target of at least 90%. Retention will be defined as the proportion of dyads that complete the study, with a target of at least 75%.

Preliminary Efficacy Outcome Measures:

Preliminary efficacy will focus on changes in activity metrics and psychosocial measures. The activity metrics will include daily step counts, daily metabolic equivalent of task, and daily average heart rate variability. These measures are pre-computed metrics on Fitabase. The psychosocial measures will include perceptions, attitudes, and practices related to physical activity, fall risk, fear of falling, functional limitations, and quality of life.

We will assess perceptions, attitudes, and practices regarding physical activity using the Perception of Physical Activity Benefits for Older Adults scale (α = 0.92), the Attitude towards Physical Activity Scale (α = 0.77), and the Physical Activity Practice Scale (α = 0.91) [53]. These perception, attitude, and practice scales each comprise 14, seven, and nine items, respectively. Higher scores on the scales indicate higher perceived benefits, a more positive attitude, and more engagement in physical activities [53].

We will define fall risk using the Stopping Elderly Accidents, Deaths, and Injuries (STEADI)—a 12-item scale (Area Under Curve: 0.91) [37,54]. Higher STEADI scores indicate higher fall risk [37,54]. Fear of falling will be measured using the 16-item Falls Efficacy Scale–International (FES-I; α = 0.96) [55]. Higher FES-I scores indicate greater fear of falling [55]. Functional limitations will be measured using the 6-item Katz Activities of Daily Living (α = 0.85) and the 8-item Instrumental Activities of Daily Living surveys (α = 0.94) [56,57]. Higher scores on these activity surveys indicate greater independence in basic and instrumental activities of daily living [56,57]. Quality of life will be assessed using the Physical and Mental Quality of Life Short Form-12 Health Survey (α = 0.87–0.90) [58]. Higher scores on the Short Form-12 indicate better physical and mental quality of life [58].

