### 2.4. Study Materials

While all surveys will be delivered using REDCap, we will use an additional six primary tools to deliver the ACTIVE intervention and obtain study data. These tools include (1.) Fitbit/Fitabase, (2.) myACTIVEsteps.com, (3.) printed educational materials, (4.) instructional education videos, (5.) physical therapy videos, and (6.) the Zoom video conferencing application.

Fitbit Inspire 3 Smartwatch and Fitabase: Participants will receive a pre-configured de-identified Fitbit Inspire 3 smartwatch to passively collect activity data, including daily step counts, activity intensity (daily duration of light, moderate, and intense physical activities), and daily heart rate variability. Fitabase, a secure HIPAA-compliant data management platform, will link each device to a study-specific dashboard and capture all transmitted Fitbit data in real time. Also, motivational text messages will be sent from the Fitabase platform to all study participants.

myACTIVEsteps.com Platform: This secure website houses all asynchronous video-guided physical rehabilitation sessions and instructional educational modules [34]. The website automatically captures engagement metrics, including logins, video access, and watch time (in minutes) for both the video-guided physical rehabilitation sessions and educational modules.

Printed Educational Materials: Care recipients and partners will receive printed copies of the Centers for Disease Control and Prevention’s fall prevention resources—“Stay Independent” [35], and “Family Caregivers: Protect Your Loved Ones from Falling” [36].

Instructional Educational Videos: Care recipients and care partners will access three-minute educational videos during the intervention period. The content of these videos was developed by the study team and is grounded in evidence-based fall prevention strategies from the Centers for Disease Control and Prevention (CDC) STEADI initiative [35,36,37]. Care recipient videos will focus on (1) benefits of moving, (2) safe home exercises, (3) fall prevention, (4) pain management, (5) building routines, and (6) long-term strength and independence. Care partners will receive parallel educational modules emphasizing (1) their role in supervision, (2) setting up safe environments, (3) recognizing risks, (4) encouraging safe activity, (5) reinforcing progress, and (6) transitioning support as independence improves.

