### 2.5. Intervention Design

The ACTIVE intervention consists of six co-occurring events as follows (Table 1):

Activity Tracking: Care recipients and their care partners will be provided with a wrist-worn Fitbit smartwatch to wear during waking hours for at least 8 h per day. Activity metrics will be tracked for care recipients and care partners on Fitabase.

Care partner co-participation: Care partners will play active, structured roles in the intervention. These roles include (1.) Safety oversight, (2.) Co-engagement, (3.) Education access and (4.) Motivation and supervision. Care partners will be required to ensure their care recipients use the smartwatch consistently, walk safely, and adhere to exercise protocols (safety oversight). They will participate in walking exercises and video-guided physical rehabilitation sessions together with their care recipient (co-participation). They will view educational videos to understand how best to support care recipients to stay active in safe environments (education). Lastly, they will encourage adherence, monitor fatigue, and help adjust routines as independence improves (motivation and supervision). Care partner engagement will be assessed using a multimodal approach, including platform-based analytics (login frequency, module completion), structured prompts embedded within myACTIVEsteps, and brief scheduled daily text message check-ins to capture real-time participation and support activities.

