Text reminders: Validated motivational text messages will be delivered to both care recipients and care partners at scheduled morning times tailored to each dyad. These messages were developed using Self-Determination Theory. They encompass nine activity-based categories: (1) exceeding the daily activity goal; (2) meeting the daily target; (3) slightly below target; (4) low activity; (5) no activity data received; (6) improvement in activity compared with the prior day; (7) decrease in activity compared with the prior day; (8) three or more consecutive days of high activity; and (9) three or more consecutive days of low activity. Details of the development and validation of the motivated text messages have been published [38]. Message delivery will be dynamically tailored based on each participant’s recorded activity from the preceding day (e.g., exceeded goal, low activity, no data, or sustained inactivity). Messages will be brief, supportive, and action-oriented, serving as daily prompts to reinforce engagement and sustained physical activity.

Instructional education: Care recipients and care partners will be assigned six brief instructional videos (2–3 min each), organized into twice-weekly educational modules delivered over the three-week intervention period. Video engagement will be automatically tracked through the myACTIVEsteps platform. A video will be considered completed if at least 70% of the total viewing time is reached.

Virtual physical therapy: Care recipients and their care partners will have access to nine evidence-based video-guided physical rehabilitation modules over three weeks—three videos per week, each lasting 10–15 min. Duration of engagement and percent completion will be tracked remotely on the website. A video session will be considered completed if at least 70% of the total viewing time is reached. We expect both care partners and their care recipients to participate in each session. At the start of each session, the user ID of the person logging in will be required, and the person will attest that the care partner/care recipient is available during the session.

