### 2.6. Intervention and Control Groups

Dyad participants randomized to the intervention arm will experience all six components of the ACTIVE intervention—Activity tracking, Care partner co-participation, Text reminders, Instructional education, Video-Guided Physical Rehabilitation, and Exercise. Dyad participants randomized to the control group will receive the Fitbit smartwatch only for physical activity tracking. They will be instructed to wear the smartwatch daily during waking hours. They will not receive motivational text messages, instructional education, or video-guided physical rehabilitation content during the intervention period. Dyad participants in the intervention and control arms may choose to discontinue participation at their own request without penalty. If either member of a dyad chooses to discontinue participation, the entire dyad will be withdrawn from the study. Participants will also be encouraged to continue their regular healthcare and daily routines.

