**Table 3 jcm-15-01341-t003:** Summary of outcome and covariate variables, including sources of data and how each measure is defined.

Outcome Measures	Analysis	Data Source
Recruitment		
1. % of dyad recruited 2. % of dyad randomized	Benchmark: ≥75%	REDCap REDCap
Adoption (measured in week 1)		
1. Smartwatch use ≥ 3 days	Benchmark: ≥75%	Fitabase
2. Motivational Texts ≥ 1 opened		Fitabase
3. Virtual PT videos ≥ 1 sessions		myACTIVEsteps
Adherence (measured weeks 1–3)		
1. Smartwatch use: % days ≥ 8 h	Benchmark: ≥75%	Fitabase
2. Videos: % sessions completed		myACTIVEsteps
3. Virtual PT: % completed		myACTIVEsteps
Acceptability (Week 5 and 9)		
1. Website SUS score 2. Virtual PT SUS Score	Benchmark: Mean ≥ 68	REDCap REDCap
1. Smartwatch TAM Score	Benchmark: Mean ≥ 4.0	REDCap
2. Motivational Texts TAM Score		REDCap
3. Educational Videos TAM Score		REDCap
4. Virtual PT TAM Score		REDCap
Fidelity (Week 5 and 9)		
1. % motivational text sent 2. % educational text notification sent	Benchmark: ≥90%	Fitabase Fitabase
Retention		
1. % of dyad completed the study	Benchmark: ≥75%	REDCap
Preliminary Effectiveness (Week 5 and 9)		
1. Activity: MET-mins/week	Linear Mixed Effect Model	Fitabase
2. FES-I score pre/post		REDCap
3. ADL/IADL score		REDCap
4. SF-12 pre/post		REDCap
5. KAP Scores–pre/post		REDCap
Covariate Measures (Assessed at Baseline)		
Sociodemographic: Age, Sex, Race/Ethnicity, Health Insurance, Education, Marital Status, Living Situation		REDCap
Health Measures: Clinical Frailty Scale, Charlson Comorbidity Index,		REDCap

PT: Physical Therapy; SUS: System Usability Scale; TAM: Technology Acceptance Model; MET: Metabolic Equivalent of Task; FES-I: Fall Efficacy Scale-International; ADL/IADL: Activities of Daily Living/Instrumental Activities of Daily Living; SF: Short Form; REDCap: Research Electronic Data Capture.

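### Prompting to wear the watch differs by arm, but steps and MET carry no wear criterion and the efficacy models no wear term, so differential wear may be read as more physical activity

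*Protocol article*

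**What the plan says.** On the outcomes, Section 2.10 states: "The activity metrics will include daily step counts, daily metabolic equivalent of task, and daily average heart rate variability". It adds: "These measures are pre-computed metrics on Fitabase". Table 3 lists the activity outcome as MET-minutes per week. No wear requirement is attached in either place.

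On wear, Section 2.5 asks for at least 8 h per day during waking hours. The threshold is used analytically in one place only, the adherence row of Table 3: "1. Smartwatch use: % days ≥ 8 h".

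On prompting, one of the nine text categories in Section 2.5 is "5) no activity data received". The care-partner component adds: "Care partners will be required to ensure their care recipients use the smartwatch consistently, walk safely, and adhere to exercise protocols (safety oversight". For controls, Section 2.6 provides the smartwatch only: "They will not receive motivational text messages, instructional education, or video-guided physical rehabilitation content during the intervention period". It also says of controls: "They will be instructed to wear the smartwatch daily during waking hours". For weeks 2–4, Table 2 places the daily texts under the intervention dyads and a weekly staff call under both arms. Section 2.4, however, says that "motivational text messages will be sent from the Fitabase platform to all study participants".

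On the analysis, Section 2.13 writes out Equations (5) and (6) and lists their fixed effects. Section 2.11 confines covariates to variables collected at enrollment. Wear time is in neither. The effect size comes from the pre-crossover phase and is meant to inform power calculations for the definitive trial.

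**The concern.** A step counter records only what happens while it is worn. If the intervention makes people wear the watch for longer, recorded steps and MET can rise while behaviour stays the same. Two intervention components act directly on wear, and controls do not receive them. Nothing in the stated outcome definition or model separates more movement from more recording.

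The contrast most exposed is the between-arm comparison over weeks 2–4, because it supplies the effect size carried forward. Any wear difference arises after randomisation, so adjusting for a baseline value would not remove it. An effect size inflated in this way would make the definitive trial too small.

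The point concerns steps and MET. It does not apply in the same way to heart rate variability, which is a daily average and need not rise with longer wear.

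**Working it through.** **The plan's own figures.** The article gives no step mean, no standard deviation and no wear hours by arm, so there is no stated figure on this point to reproduce. The one precision calculation, in Section 2.8, reproduces: √(0.75 × 0.25/100) = 0.043; × √1.2 = 0.047; 0.75 ± 1.96 × 0.047 = 0.66 to 0.84. The present point does not depend on it.

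**Can the stated methods absorb a wear difference?**

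- *Whole days unworn.* Section 3 says that forgetting to wear or charge the watch may introduce missing data, and Section 2.13 plans multiple imputation and mixed models. If such days are set to missing, and the missingness is unrelated to activity, the daily mean is not biased.
- *Days partly worn.* These yield a recorded but low value. Imputation and mixed models act on absent values, so they leave it unchanged.
- *Weekly MET-minutes.* A weekly sum falls with each unworn day unless it is divided by the number of worn days.

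**Size, with no true effect.** All wear figures below are assumptions. Let T be true activity, equal in both arms, and w the share recorded. Recorded activity is T × w, and the spurious ratio is w(intervention)/w(control).

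| Wear, control v intervention | Ratio |
|---|---|
| equal, e.g. 75% v 75% | 1.00 |
| 85% v 90% | 0.90/0.85 = 1.06 |
| 75% v 85% | 0.85/0.75 = 1.13 |
| 75% v 90% | 0.90/0.75 = 1.20 |
| reversed, 85% v 75% | 0.75/0.85 = 0.88 |

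*Partly worn days*, with T = 5000 steps spread evenly over 14 waking hours (difference = 5000 × gap in hours/14):

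| Hours worn, control v intervention | Spurious steps/day | Ratio |
|---|---|---|
| 12 v 13 | 5000 × 1/14 = 357 | 13/12 = 1.08 |
| 12 v 14 | 5000 × 2/14 = 714 | 14/12 = 1.17 |
| 10 v 12 | 5000 × 2/14 = 714 | 12/10 = 1.20 |

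*Unworn days*, 75% v 85% of days worn: if they count as zero, 5000 × (0.85 − 0.75) = 500 steps/day, ratio 1.13. An undivided weekly sum has the same ratio, because the seven days cancel. If they are missing and unrelated to activity, the difference is 0.

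*Standardised*, for an assumed SD of 2000–3000 steps: 357 gives 0.12–0.18 (357/3000 to 357/2000), 500 gives 0.17–0.25, and 714 gives 0.24–0.36.

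**Planning consequence.** Required sample size varies as 1/(effect)². If the true effect were as large as the artefact, the estimate would be doubled and the planned size would be (1/2)² = one quarter of what is needed.

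**Does an 8 h rule suffice?** It removes short days and settles unworn days. Days of 10, 12, 13 and 14 h all pass, so the 357–714 step differences in the second table would remain.

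**The case against.** A reader might infer that the platform values will be analysed exactly as delivered, that unworn days enter as low totals, and that the effect is certain to be biased upward. The documents do not support this.

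- Saying that the metrics are pre-computed states who calculates them, not that short-wear days are kept. A detailed valid-day rule can reasonably sit in a full protocol or SAP that is not shown.
- The article points to unworn days being missing. Section 3 describes forgotten wear as missing data, and the text categories in Section 2.5 separate no data from low activity. The no-data text responds to exactly those days, so on its own it need not create bias. The care-partner duty is the stronger support.
- Both arms have a wear instruction and weekly calls, and Section 2.9 does not limit monitoring and reminders to one arm. These may narrow any gap.
- Section 2.4 has texts going to everyone. That may only reflect the crossover, but it sits awkwardly with Section 2.6 and Table 2.
- The pilot is stated not to be powered for efficacy.

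All of this stands against certainty and against any claimed size. It does not dispose of the point. The article is not merely silent: it sets a wear threshold, assigns it to adherence alone, names a weekly MET outcome, and writes out the efficacy models without a wear term. Partly worn days are outside its missing-data plan. The lack of efficacy power does not help either, because the effect estimate is what is carried forward.

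**Conclusion.** The point holds as a risk, not as a demonstrated bias. Wear prompting differs by arm by design, and the stated outcomes and models could turn a wear difference into an apparent effect on steps and MET in the weeks 2–4 contrast. Treating unworn days as missing limits this but leaves partly worn days and unnormalised weekly totals exposed.

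The size and direction of any wear difference are unknown. The artefact is 0% with equal wear, about 6–20% for the assumed gaps favouring the intervention, and negative if the gap runs the other way. These figures assume equal true activity and recorded totals proportional to wear. It is worth correcting now because the correction is cheap and the estimate has a planned use.

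**What to change.** In Sections 2.10 and 2.13 and Table 3:

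1. For steps and MET, in both conditions, count a day only if wear is at least 8 h, the threshold already in Table 3. Set other days to missing, never to zero.
2. Analyse means per valid day rather than unnormalised weekly totals, and settle whether the MET outcome is daily (Section 2.10) or weekly (Table 3).
3. Report wear hours and numbers of valid days by condition.
4. Add a sensitivity analysis of steps or MET per worn hour, or adjusted for wear hours, because the 8 h rule leaves differences above 8 h untouched.
5. Show results with and without the valid-day rule.
6. Reconcile Section 2.4 with Section 2.6 and Table 2 on who receives the texts and when.

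The cost is wording and some dropped days. Wear hours are already needed for the adherence outcome, so no new data are required. The filter and the adjustment both condition on a variable measured after randomisation that treatment may affect, and so could introduce selection of their own. That is why item 5 is needed and why wear adjustment belongs in a sensitivity analysis.

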### 2.11. Covariates

Covariates will include sociodemographic and health survey data collected from the older adult and care partner at enrollment. This sociodemographic and health survey includes age, sex, race/ethnicity, education, insurance status, marital status, living situation, the Clinical Frailty Scale score [59,60], and the Charlson Comorbidity Index [61,62]. AD/ADRD status (mild AD/ADRD vs. no AD/ADRD) will be used as a stratification variable.

### 2.12. Data Collection by Study Phase

At baseline, dyads will complete sociodemographic and health surveys and background efficacy measures (Figure 2). During the mid-intervention assessment (intervention arm only), care recipients and care partners will repeat all baseline surveys (excluding the sociodemographic and health surveys) and additionally complete the revised Technology Acceptance Model and the System Usability Scale. At the crossover phase, selected dyads who began in the intervention arm will participate in qualitative interviews. At the end-of-study assessment, dyads who completed the delayed intervention will repeat all surveys, and some will be selected for qualitative interviews.

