### 2.7. Study Procedure

The study will run for 10 weeks (Figure 2), starting with a one-week pre-intervention phase, followed by three weeks of intervention (or control), one week crossover phase, three weeks of control (or intervention), and a two-week post-intervention phase. The 3-week intervention period was selected to balance feasibility assessment with participant burden, consistent with pilot study methodology [39,40]. This duration provides adequate time to evaluate key feasibility outcomes while generating preliminary effect estimates to inform sample-size calculations for a definitive trial. Prior digital health intervention pilots have used a similar intervention period to assess the feasibility of technology-based interventions [41,42,43].

Week 1 (Pre-Intervention): The study team will call the dyad to confirm receipt of the study materials and ensure: (1) the appropriate wearing of the Fitbit smartwatches and data capture, (2) receipt of motivational text messages, and (3) access to the educational videos (Table 2). Data collected during this week will not be used for the study.

Weeks 2–4 (Phase I Intervention/Control): The intervention will start with dyads randomized to the intervention arms. Remote tracking of physical activity data will continue in the control arm.

Week 5 (Crossover/Washout): Participants will switch arms (intervention to control and vice versa). Activity data during this crossover week will not be analyzed (Table 2). Participants in the intervention arm will complete six post-intervention surveys (discussed below), and a few will participate in interviews.

Weeks 6–8 (Phase II Intervention/Control): Participants will continue in their new assignments (opposite of initial condition).

Weeks 9–10 (Post-Intervention): Crossover participants in the intervention arm will undergo post-intervention surveys and interviews. All participants will have access to the educational videos and video-guided physical rehabilitation sessions upon completion of the study (Table 2).

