Preliminary Efficacy Assessment: Using linear mixed-effects models, we will estimate the effect size of the ACTIVE intervention’s preliminary efficacy on the three activity metrics and seven post-intervention behavioral measures (listed above). The effect size will be estimated from the pre-crossover phase (Equation (5)). Full six-week mixed-effects models are used to evaluate whether longitudinal patterns remain consistent with the pre-crossover estimate, after accounting for the impact of the crossover and the sequence of intervention (Equation (6)). The random intercept will account for both within-dyad correlation and repeated measures. Fixed effects will include treatment (intervention vs. control), sequence (intervention first or last), baseline values of the outcomes, dementia status (mild AD/ADRD vs. no AD/ADRD), treatment × dementia interaction, period (pre-crossover vs. post-crossover), treatment × period interaction, and covariates to assess potential differential effects. For participant *i* in dyad *d* at time *t* (t = baseline, follow-ups), the outcome will follow the mixed effect model in Equations (1) and (2), as follows:(5)$${\;Y}_{idt}=\;\beta_{0}+\;\beta_{1}{Trt}_{i}+\;\beta_{3}{Time}_{t}+\;\beta_{5}Y_{id0}+\;\beta_{6}{Dem}_{i}+\;\beta_{7}\left({Trt}_{i}\;\times \;{Dem}_{i}\right)+\;\tau^{T}X_{i}+\;b_{d}+\;b_{i\left(d\right)}+\;\in_{idt}\;\;$$(6)$$Y_{idt}=\beta_{0}+\beta_{1}{Trt}_{i}+\beta_{2}{Seq}_{i}+\beta_{3}{Time}_{t}+\beta_{4}{Period}_{t}+\beta_{5}Y_{id0}+\beta_{6}{Dem}_{i}+\beta_{7}\left({Trt}_{i}\times {Dem}_{i}\right)+\beta_{8}\left({Trt}_{i}\times {Period}_{i}\right)+\tau^{T}X_{i}+b_{d}+b_{i(d)}+\in_{id\;\;\;\;\;\;\;\;}$$

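### Follow-up surveys are taken only after the intervention, so the seven survey outcomes have no control follow-up and their treatment effect cannot be estimated

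*Protocol article*

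**What the plan says.** All dyads complete the efficacy surveys at baseline (Section 2.12). After that, two sections of the protocol article tie the surveys to exposure.

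- **Week 5.** Section 2.12: "During the mid-intervention assessment (intervention arm only), care recipients and care partners will repeat all baseline surveys". Section 2.7, independently: "Participants in the intervention arm will complete six post-intervention surveys".
- **Weeks 9–10.** Section 2.12: "At the end-of-study assessment, dyads who completed the delayed intervention will repeat all surveys". Section 2.7: "Crossover participants in the intervention arm will undergo post-intervention surveys and interviews".

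Section 2.13 will fit linear mixed-effects models to "the three activity metrics and seven post-intervention behavioral measures". It takes the effect size from the pre-crossover phase through Equation (5), with intervention versus control as a fixed effect. Equation (6), fitted over the full six weeks, is the consistency check. The effect sizes are meant to inform power calculations for the definitive trial.

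**The concern.** A randomised effect needs a follow-up measurement in both arms. Control-first dyads are not surveyed at week 5, when their control phase has just ended. Intervention-first dyads are not surveyed at weeks 9–10, when theirs has. The survey data would then hold no control-condition follow-up at all.

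This affects perceptions, attitudes, practices, fall risk, fear of falling, functional limitations and quality of life. For these, an intervention effect could not be separated from the passage of time, retesting, wearing the watch or the weekly staff calls that both arms receive. The within-participant comparison that the Discussion credits to the crossover would not exist for them either. A standardised effect carried from here into the definitive trial's sample size would be a before-after change presented as a randomised contrast.

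**Working it through.** **The plan's own figure.** Section 2.8 gives one computed design figure, which reproduces. SE = √(0.75 × 0.25 / 100) = 0.0433. With ICC 0.2 and cluster size 2 the design effect is 1.2, so the adjusted SE is 0.0433 × √1.2 = 0.0474. The interval is 0.75 ± 1.96 × 0.0474 = 0.657 to 0.843, as stated (0.66–0.84). The concern does not depend on it.

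**Survey records under the schedule as written** (50 dyads, about 25 per sequence, two people each):

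| Time | Intervention-first (about 50 people) | Control-first (about 50 people) |
|---|---|---|
| Baseline | surveyed | surveyed |
| Week 5 | surveyed, just after intervention | not surveyed |
| Weeks 9–10 | not surveyed | surveyed, just after intervention |

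Control-condition follow-up records: 0 of 50 in Phase I and 0 of 100 over the study.

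**Equation (5), fixed effects.** The columns are intercept, Trt, Time, baseline value, Dem, Trt × Dem and one illustrative covariate: seven in all.

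1. *Follow-up rows only.* Every row has Trt = 1, so Trt equals the intercept, Trt × Dem equals Dem, and Time is constant. The rank is 4 of 7 and β₁ is not estimable.
2. *Baseline rows kept as responses, Trt set to 0 at baseline.* Trt changes only when Time does, so the two are collinear. The rank is 6 of 7 and β₁ is not estimable.
3. *Baseline rows kept, Trt coded as assigned arm,* which is how the participant-level subscript in Equation (5) reads. The rank is 7 of 7 and the model runs. Control rows exist only at baseline, so the Time coefficient absorbs the whole change in the intervention arm. β₁ is left with the between-arm difference at baseline, where the response is its own covariate. In simulation with a true effect of 0.5 SD, the mean estimate of β₁ was −0.001. Software would report a null effect without any warning.

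**Equation (6), fixed effects.** On follow-up rows, Trt equals the intercept and Trt × Dem equals Dem. Seq, Time and Period all carry the same single distinction (first sequence at week 5, second at week 9), and Trt × Period equals Period. Intercept, Trt, Seq, Time, Period, Dem, Trt × Dem and Trt × Period have rank 3 of 8. With the baseline value and one covariate added, the rank is 5 of 10. With baseline rows it is 8 of 10. β₁ is not estimable in any of these. Dropping both period terms makes it computable, but only by assuming a linear time trend across weeks 5 and 9 with no concurrent control.

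**With both arms surveyed at week 5.** There are 50 intervention and 50 control records, and β₁ in Equation (5) is estimable. The standardised mean difference, averaged over the dementia strata, has SE = √(2 × 1.2 / 50) = 0.219 SD, and 1.96 × 0.219 = 0.43 SD. Over the protocol's ICC range of 0.1 to 0.3 the half-width is 0.41 to 0.45. At the 75% retention benchmark (37.5 people per arm), SE = √(2 × 1.2 / 37.5) = 0.253 and the half-width is 0.50 SD (0.48 to 0.52).

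**The case against.** The strongest reply is that the sponsor may intend to survey everyone. Table 2 labels content that belongs to one arm, but its week 5 and weeks 9–10 entries list interviews and surveys with no arm label. Table 3 places the efficacy measures at weeks 5 and 9 without naming an arm. The planned contrast only makes sense if controls are surveyed, and Figure 2, which holds the schedule, is not available here. This stands as a caveat about intent. It does not remove the defect: neither table says that control dyads are surveyed, while four statements in Sections 2.7 and 2.12 say who is. On either reading those sections must be corrected.

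A second reply is that this is a pilot, not powered for efficacy, with a go/no-go rule that uses feasibility benchmarks only. The rule is indeed untouched, and so are the Fitbit metrics, because tracking continues under control. But the problem is identification, not power: more dyads on the same schedule would not help, and the effect sizes are explicitly wanted for the next trial.

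A third is that mixed models or multiple imputation deal with incomplete data. They need some observed control follow-up to learn from, and here there is none by design. A separate analysis plan cannot supply data that are not collected.

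One limit of the remedy is real. Even with everyone surveyed at both times, Equation (6) has rank 8 of 10 on follow-up rows alone. Extra surveys do not by themselves restore that check.

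**Conclusion.** The concern holds for the schedule as Sections 2.7 and 2.12 state it. For all seven survey outcomes the planned intervention-versus-control effect cannot be estimated from Equation (5) or Equation (6). The one coding that runs, in Equation (5), returns a coefficient near zero whatever the true effect. Only an uncontrolled before-after change in each sequence remains.

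This rests on reading the four statements literally and on Figure 2 not contradicting them. The non-estimability itself needs no assumption about variances or ICC. The 0.43 SD half-width after correction assumes 25 dyads per arm, equal SDs, ICC 0.2, complete follow-up and no gain from baseline adjustment. It should be corrected before control-first dyads pass week 5, because that measurement cannot be recovered once they start the intervention.

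**What to change.** 1. In Sections 2.7 and 2.12, have all dyads complete the efficacy surveys at week 5 and again at weeks 9–10. Control-first dyads should finish the week-5 survey before any intervention content is released to them. Keep the System Usability Scale and the Technology Acceptance Model for dyads that have just used the tools. Make Tables 2 and 3 and Figure 2 say the same.
2. In Section 2.13, estimate the survey effects from the randomised week-5 comparison: week-5 score on assigned arm, baseline score, dementia status, the planned interaction and covariates, with a dyad random intercept. With one follow-up row per person, Time is constant and the individual random intercept cannot be separated from the residual, so both drop out. Do not enter baseline both as a response and as a covariate.
3. If the schedule cannot change, describe the seven measures as uncontrolled before-after change and do not use them as treatment effects for the definitive trial.

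**Cost.** An IRB amendment with a registry update as applicable, and about 100 extra remote REDCap completions: 50 control-first people at week 5 and 50 intervention-first people at weeks 9–10. The first 50 are what the randomised contrast needs. The second 50 describe maintenance after the intervention is withdrawn. The added burden is one survey round per dyad.
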